### Secondary Hypotheses and Outcomes

Participation in the intervention group is expected to improve treatment satisfaction, therapy adherence, and detection and timely treatment of critical AEs. The close-meshed, weekly, brief HRQoL assessment was tested as a screening tool to detect relevant side effects during therapy. The study provides HRQoL objectivity across treatment strategies. In addition, a usability and feasibility analysis of the app and the intervention concept was carried out.

### Inclusion Criteria

The inclusion criteria are as follows: diagnosis of invasive breast cancer or metastasis of breast carcinoma; 18 years or older; fluency in German; access to a computer, tablet, or smartphone with internet connectivity; capacity to provide informed consent; and a signed informed consent form.

### Data Acquisition and Management

The study is based on the principles of the Declaration of Helsinki. The study plan and all other study-relevant documents were approved by the ethics committees of the university medical faculties of Heidelberg, Mannheim, and Tuebingen, Germany. The current version of the study protocol is 4.2 from December 9, 2022. Protocol amendments were communicated to participating centers immediately. The study participants have the right to request information about the personal data collected from them. Participation in the study is voluntary after all study content and objectives have been declared and written consent has been given and can be terminated at any time without any disadvantages for the patient.

Patient data and clinical data are recorded pseudonymously and stored centrally in the electronic case report form (eCRF). The data were documented from the medical reports and tumor documentation of the treating center in a web-based eCRF via the study staff at the study centers. These eCRFs are stored and managed throughout the duration of the study in a secured cloud infrastructure, which was conceptualized and initiated by the Institute of Women’s Health GmbH and the three partner sites of the Center for Innovative Care in Heidelberg, Mannheim, and Tuebingen. This high-availability infrastructure guarantees and verifies individual permission rights and user roles for all participating clinicians for strict compliance with data protection regulations. For future research, all accumulated data will be transferred into the individual clinic infrastructures after the study ends, and all externally hosted data will be permanently erased. An interim analysis of the secondary end points was conducted after 50% of the patients had been included and carried out by the Institute of Women’s Health GmbH. The data monitoring committee is made up of the principal investigators from the Heidelberg and Tuebingen centers and is independent of the sponsor of the study.

The following clinical data are recorded: demographic data, Eastern Cooperative Oncology Group status, height, weight, stage of the disease, previous diseases, clinical tumor characteristics, tumor biology, staging results, therapy-associated side effects, and previous and current therapies.

### Sample Size Calculation

The sample size was calculated according to the primary end point HRQoL (measured via the PROMIS-29). It was based on a minimal important difference of 5 points, an SD of 10 points, a power of 80%, a 2-sided significance level of 5%, and a dropout rate of 37.5%. PASS (NCSS, LLC) software was used to calculate the sample size.

### Statistical Analysis

The primary outcomes will be examined in an intention-to-treat analysis for all randomized individuals with a mixed linear regression model. Primary analysis will be adjusted for age, therapy situation, type of systemic therapy, Eastern Cooperative Oncology Group status at enrollment, and other important confounders if necessary. The heterogeneity between the trial sites is considered through random effects (random intercept mixed model). The level of significance is set at α=5%.

All secondary outcomes will be analyzed analogously to the primary hypothesis and according to the respective outcome using further suitable statistical methods. As in the analysis of the primary outcome, the secondary hypotheses will be adjusted for relevant confounders. In addition, the heterogeneity between study centers will be considered. Secondary outcome analysis will be performed exploratively.

All statistical analyses will be planned in detail and documented in a statistical analysis plan that will be prepared before closing the database.

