## Methods

### Study Design

Patients were included before starting systemic therapy for breast cancer in neoadjuvant, adjuvant, postneoadjuvant, and palliative treatment settings. Patients were recruited at the respective oncology centers. The study randomized patients 1:1 into an intervention and a control group. In both groups, QoL was assessed for at least six fixed time points during therapy using European Organization for the Research and Treatment of Cancer Quality of Life Questionnaire-C30, European Organization for the Research and Treatment of Cancer Quality of Life Questionnaire-BR45, and Patient-Reported Outcomes Measurement Information System-29 (PROMIS-29; Figure 1). Participating centers are the university hospitals of Heidelberg, Tuebingen, and Mannheim, Germany.

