### Primary Hypothesis and Outcome

The primary end point of the study is to compare HRQoL and treatment satisfaction (measured by the PROMIS-29) between the intervention and control groups.

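### The covariates named for the primary mixed model omit the baseline PROMIS-29 score, which gives away precision and leaves chance baseline imbalance uncorrected

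*Protocol article*

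**What the plan says.** The primary end point (Primary Hypothesis and Outcome) is to "compare HRQoL and treatment satisfaction (measured by the PROMIS-29) between the intervention and control groups". The Statistical Analysis section plans an "intention-to-treat analysis for all randomized individuals with a mixed linear regression model". For covariates it says: "Primary analysis will be adjusted for age, therapy situation, type of systemic therapy, Eastern Cooperative Oncology Group status at enrollment", followed by "and other important confounders if necessary". On random effects it says: "The heterogeneity between the trial sites is considered through random effects (random intercept mixed model". No patient-level random effect is named, and nowhere does the article describe the outcome as a change from baseline. Further detail is to be "documented in a statistical analysis plan that will be prepared before closing the database".

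Under Study Design, "Patients were included before starting systemic therapy for breast cancer". The same section lists PROMIS-29 among the questionnaires given to both arms at six or more fixed time points.

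**The concern.** In a trial with a quality-of-life outcome, a patient's own starting score usually explains more of the later score than age or performance status does. That is a general statistical expectation; the article reports no correlation. Here the model names age, therapy and ECOG status but gives the starting PROMIS-29 score no way in, either as a covariate, through a change score or through a patient-level term.

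Two things are at stake. The treatment effect is estimated with a wider interval than the data allow. And if the arms differ by chance in HRQoL at the start, that difference carries over into the primary estimate in proportion to the baseline-to-follow-up correlation.

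Two smaller points arise in the same sentence. The words fixing a covariate at enrolment stand directly after ECOG status, so it is unclear whether they also cover therapy situation and type of systemic therapy. And the clause on further confounders has no rule for when it applies.

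**Working it through.** **Inputs from the protocol article.** Difference: "minimal important difference of 5 points". SD 10 points, power 80%, two-sided alpha 5% and dropout 37.5% (all Sample Size Calculation). Allocation 1:1 (Study Design). 606 enrolled, 592 remaining after 14 did not complete app setup (Results).

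**Input assumed.** Baseline-to-follow-up correlation r. The article gives none, so the range 0.3 to 0.7 is shown.

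**Step 1: what the stated inputs require.** The article gives no target N to reproduce. By the normal approximation, n per arm = 2 × (1.960 + 0.842)² × 10² / 5² = 62.8, so 63 per arm and 126 in total. With dropout, 126 / 0.625 = 201.6, so 202. The t-test version gives 64 per arm, 128 in total, and 205 with dropout.

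**Step 2: precision and power without the baseline score.** Completers: 592 × 0.625 = 370, or 185 per arm.
- SE = 10 × √(2/185) = 1.04 points.
- 95% CI half-width = 1.96 × 1.04 = 2.04 points.
- Power for 5 points = Φ(5/1.04 − 1.96) = Φ(2.85), about 99.8%.

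Starting from 606 instead gives about 189 per arm and the same power to one decimal.

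**Step 3: with the baseline score as a covariate.** Residual SD = 10 × √(1 − r²). Half-width = 1.96 × residual SD × √(2/185).

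| r | Variance removed (r²) | Residual SD | 95% CI half-width at 185 per arm |
|---|---|---|---|
| none | 0% | 10.00 | 2.04 |
| 0.3 | 9% | 9.54 | 1.94 |
| 0.5 | 25% | 8.66 | 1.76 |
| 0.7 | 49% | 7.14 | 1.46 |

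**Step 4: chance imbalance.** If the baseline SD is also 10 (assumed), the difference in mean baseline score between two arms of 185 has the same SE of 1.04. An imbalance of 2.04 points or more then occurs by chance in about 1 trial in 20. An imbalance of exactly 2.04 points moves an estimate without baseline adjustment by r × 2.04: about 0.6 points at r = 0.3 and 1.4 points at r = 0.7. Over repeated randomisations these shifts average to zero.

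**Limits of the calculation.** The factor 1 − r² compares with a model that has no covariates and a single follow-up score. Age, therapy and ECOG status are already in the model and may carry part of what the baseline score explains, so the variance reductions are upper figures for each r.

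**The case against.** The strongest reply is that this is a condensed article and that a statistical analysis plan, not shown, is to follow. Baseline handling, the visits in the contrast and the final covariate list commonly belong there, and the clause on further confounders leaves room for the baseline score. This stands in part: the plan may already contain the fix. But the article does not simply defer covariates. It names four and leaves out the one most directly tied to the outcome, and that published list is what readers will compare with the results.

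Several stronger readings are tempting, and the article does not support them.

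- **Bias or lack of power.** Under 1:1 randomisation, leaving out baseline does not bias the comparison in expectation, and Step 2 shows ample power for the planned difference.
- **Dilution of the effect by a pre-intervention visit counted among the outcomes.** This needs a known visit schedule and a rule that averages all visits into one group effect. Figure 1 is not shown, the assessments are described as taking place during therapy, and no averaging rule is stated.
- **Adjusting away part of the effect through therapy as later received.** The enrolment wording can be read as covering the whole list, patients enter before therapy, and the Care Team Web App section has them assigned to a treatment and care plan through the platform by which they are included. Nothing says that later therapy will be used. This is an ambiguity only.
- **Covariates chosen after seeing results.** The article states no such choice and promises a detailed plan before database closure. The clause is loose, and closing it is largely a matter for that plan.

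**Conclusion.** The point holds as a low-cost improvement to the primary analysis. As stated, the model omits the baseline PROMIS-29 score and names only a site random effect, so it loses precision and does not correct chance imbalance in starting HRQoL. The loss depends on a correlation that the article does not report: small at 0.3 and substantial at 0.7, with the half-widths in the table as the best case for each value. No conclusion at the planned 5-point difference is threatened; the benefit is a tighter estimate and protection against an unlucky allocation.

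Two assumptions carry this. First, the first fixed assessment falls at or before the start of therapy. Second, it is completed before the intervention can act. The Figure 2 caption places randomisation at enrolment in the care portal, so the order of allocation and first questionnaire should be checked.

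**What to change.** In the analysis plan, before the database is closed:

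1. Add the first, pre-therapy PROMIS-29 score as a fixed covariate in the primary model, or use a longitudinal model that constrains the baseline means of the two arms to be equal.
2. Base the treatment contrast on post-baseline assessments only.
3. State a simple rule for patients without a baseline score, applied identically in both arms, so that all randomised patients with follow-up stay in the analysis. The constrained-baseline model handles most of this itself.
4. As a minor clarification, state that therapy situation and type of systemic therapy are those planned at enrolment.
5. Limit the clause on further confounders to prespecified sensitivity analyses.

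The cost is a few lines of text. Provided the first fixed assessment is the pre-therapy one, no new data are needed.

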### Ethical Considerations

The study was approved by the central ethics committee in Heidelberg (S-658/2020). All recruiting centers obtained approval from the local ethics committees (Ethics Committee at the Medical Faculty of the Eberhard Karls University of Tuebingen and the University Hospital of Tuebingen: 896/2020BO2; Ethics Committee II of the University of Heidelberg, Mannheim Medical Faculty: 2021-544) before study initiation. Written informed consent was obtained from all participants before study participation. The authors affirm that human research participants provided informed consent for publication. Patients signed informed consent regarding publishing their data. Participants received no financial or other compensation for their involvement in the study.

## Results

Recruitment started on March 22, 2021, in Heidelberg; April 11, 2021, in Tuebingen; and November 4, 2021, in Mannheim. The last patient was enrolled on September 8, 2023, and the last visit was in February 2024. Due to the innovative specifications of the app, the protocol was only published after the recruitment phase was completed. The protocol was submitted before the end of data collection. A total of 606 patients were enrolled in the study; however, 14 patients did not complete the app’s initial setup process and were therefore excluded from the trial. The remaining 592 patients included in the trial consisted of 380 (64.2%) patients who received neoadjuvant chemotherapy, 138 (23.3%) patients who underwent adjuvant chemotherapy, 38 (6.4%) patients who received adjuvant endocrine therapy, 12 (2%) patients who underwent postneoadjuvant therapy, and 4 (0.7%) patients who received palliative chemotherapy. The first results are expected to be published in Q2 2025.

## Discussion

### Principal Findings

Study results published in the last few years have already demonstrated the many possibilities for increasing the quality of care, treatment, and HRQoL in breast cancer treatment due to patient-reported outcome measurements (PROMs), and survival rates have improved, too [21,22]. These results fundamentally underscore the necessity of consistently integrating eHealth and telemedicine, particularly in the context of electronic patient-reported outcome measurement, into breast cancer therapy.

However, some barriers to implementing eHealth in mainstream care remain. Among the theoretical aspects is the fact that no standard has been established yet either for selecting questionnaires or for downstream interventions. One task for the coming years will be to develop basic items and a basic dataset in order to establish a system for quality control and to make it possible to compare the collected data.

For the purpose of standardizing the PROMs for a value-based PRO, the “International Consortium for Health Outcomes Measurement” has defined a minimal standard PRO Set [26]. In addition, the “Innovative Medicines Initiative—Health Outcomes Observatory” (H2O) consortium has developed core outcome sets to make HRQoL in patients with metastatic breast cancer more objective [27]. However, there is still no standard PROMs for PRO-based interventions in oncology.

In principle, we need to determine which intervals between assessments and for how long eHealth monitoring—in the sense of a PROM—are useful for patients with breast cancer. These questions need to be addressed in clinical studies, while simultaneously striving to integrate the findings from individual studies. Only then can PROMs be sensibly implemented in standard care. At the same time, different apps and providers must be able to access these interfaces, and we must also be able to transfer downstream interventions to a common system. Otherwise, implementation in everyday life could fail due to the abundance of additional documentation work required and the cost of developing additional software and apps.

The ongoing digitalization of all areas of life will ensure that there is no way back to less digitalized health care. However, despite all considerations of progress, the patient must never be left out of the focus of these efforts. Digitalization and the use of eHealth must always be based first and foremost on improving patient care and should never be an end in itself. The possibility to aggregate data through eHealth apps must also be weighed very critically in terms of scientific benefit and burden for the patient.

The ENABLE study aims to investigate the impact of a PRO-based intervention in different treatment settings for breast cancer. Recently, Karsten [28] presented findings at the San Antonio Breast Cancer Symposium demonstrating the beneficial effects of PRO-based interventions on fatigue, physical functioning HRQoL, and overall survival in the metastatic setting, too, underscoring the importance of bringing PRO monitoring into the standard of care for advanced breast cancer. These findings align with other positive PRO intervention studies in metastatic breast cancer that found improved therapy adherence, delayed onset of serious AEs, reduced toxicity, fewer unplanned hospitalizations, increased patient satisfaction, and enhanced HRQoL [29-31].

### Conclusions

The impact of neoadjuvant and adjuvant chemotherapy on HRQoL has not yet been thoroughly investigated. It is particularly important to explore the extent to which a PRO-based intervention may also positively influence patients’ HRQoL and symptoms in the adjuvant setting. Pappot et al [24] could not show a significant impact of a PRO-based intervention on treatment adjustments, unplanned hospitalization, or febrile neutropenia in a cohort of patients with breast cancer undergoing adjuvant therapy. Therefore, beyond its primary end point, the ENABLE study offers the opportunity to examine the effects of the intervention and the HRQoL on therapy outcomes, adherence, and AEs.

## Abbreviations

AE: adverse event
eCRF: electronic case report form
HRQoL: health-related quality of life
PRO: patient-reported outcome
PROM: patient-reported outcome measurement
PROMIS-29: Patient-Reported Outcomes Measurement Information System-29
QoL: quality of life
RPA: reactive patient-reported outcome assessment
